## Treatment description

Not applicable. No drug is evaluated in either of the two groups.

# Variables and measuring instruments

## Diagnostic criteria for the pathologies under study.

Unstable angina. This is a clinical syndrome that presents with chest pain in response to myocardial ischaemia, associated or not with ST-segment depression or elevation or T-wave inversion, transiently, without elevation of troponin or CK-MB.

NSTEACS. Clinical syndrome of ischaemic chest pain together with ST-segment depression or elevation or T-wave inversion, transient but somewhat more persistent, with troponin or CK-MB elevation.

STEACS. A clinical syndrome of chest pain secondary to myocardial ischaemia associated with persistent ST-segment elevation and elevated troponin or CK-MB.

## Measuring instruments

**A. Analytical data**

Glucose, creatinine, total cholesterol, LDL cholesterol, HDL cholesterol, triglycerides, CRPus, HbA1c

**B. Survey**

**a. Questionnaire on adherence to the Mediterranean diet:**

| **1** Do you use olive oil as your main cooking fat? | Yes | 1 point |
| --- | --- | --- |
| **2** How much olive oil do you consume in total per day (including frying, eating out, salads, etc.)? | 2 or more tablespoons | 1 point |
| **3** How many servings of vegetables do you eat per day (1 serving = 200g. Garnishes or side dishes are equivalent to  ½ portion)? | 2 or more (at least 1 of them in raw salad) | 1 point |
| **4** How many pieces of fruit (including fruit juice) do you eat per day? | 3 or more | 1 point |
| **5** How many portions of red meat, hamburgers, sausages or cold meats do you eat per day (1 portion = 100-150 g)? | Less than 1 | 1 point |
| **6** How many servings of butter, margarine or cream do you consume per day (single portion = 12 g)? | Less than 1 | 1 point |
| **7** How many carbonated and/or sweetened beverages (soft drinks, colas, tonic, bitters) do you consume per day? | Less than 1 | 1 point |
| **8** Do you drink wine and how much every week? | 3 or more glasses | 1 point |
| **9** How many portions of pulses do you consume per week (1 plate or  portion = 150 g)? | 3 or more | 1 point |
| **10** How many portions of fish/seafood do you consume per week (1 plate, piece or portion = 100-150 g fish or 4-5 pieces or 200 g seafood)? | 3 or more | 1 point |
| **11** How many times do you eat commercial confectionery (not homemade,  such as biscuits, custards, sweets, pastries, cakes) per week? | Less than 3 | 1 point |
| **12** How many times do you eat nuts and dried fruit per week (1 portion = 30 g)? | 1 or more | 1 point |
| **13** Do you prefer chicken, turkey or rabbit meat to beef, pork, hamburger or sausage (chicken, turkey or rabbit: 1 piece or portion 100-150 g)? | Yes | 1 point |
| **14** How many times a week do you eat cooked vegetables, pasta, rice or other dishes seasoned with tomato, garlic, onion or leek sauce simmered with olive oil (sofrito)? | 2 or more | 1 point |

Assessment:

a. If the result is equal to or less than 8 points >>>> it is in your interest to improve.

b. If the result is between 9-12 points >>> you are doing well although you can still improve

c. If the result is 13 or 14 points >>> continue in the same direction.

**b. HAD Questionnaire. Hospital, anxiety, depression**

This test is intended to determine how you have been feeling in the last week, although the questions are in the present tense. You have to choose between one of four possibilities regarding the question asked, circling the chosen answer. (A = Anxiety) (D = Depression)

1. I am tense or nervous (A)

(0) Never A

(1) Sometimes

(2) Many times

(3) Everyday

1. I still enjoy what I once loved (D)

(0) Never D

(1) Sometimes

(2) Many times

(3) Everyday

1. I have a feeling of fear, as if something horrible was about to happen (A)

(0) Never A

(1) Sometimes

(2) Many times

(3) Everyday

1. I can laugh and see the bright side of things (D)

(0) Never D

(1) Sometimes

(2) Many times

(3) Everyday

1. I am full of worries (A)

(0) Never A

(1) Sometimes

(2) Many times

(3) Everyday

1. I feel happy (D)

(0) Never D

(1) Sometimes

(2) Many times

(3) Everyday

1. I can sit quietly and feel relaxed (A)

(0) Never A

(1) Sometimes

(2) Many times

(3) Everyday

Assessment:

1. If the result is between 0 and 7 it does not indicate a case of either anxiety or depression.

b. If the result is between 8 and 10 it would be a doubtful case.

c. If the result is above 11 it is probably a case in each of the subscales.

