## Secondary Objectives

Verify the improvement of the following parameters after the intervention:

A. Stress test:

● Demonstrate increase in VO2max.

● Demonstrate increase in exertion time.

● Demonstrate increase in workload.

● Decrease the presence of symptoms.

B. Analytical:

● Obtain improvement in lipid profile.

● Decrease in CRPus.

C. Lifestyle:

● Demonstrate increased adherence to Mediterranean diet.

● Demonstrate improved outcomes in psychological state.

● Demonstrate increased willingness to quit smoking and smoking cessation.

● Demonstrate a decrease in the sedentary lifestyle indicator.

● Demonstrate an earlier return to work.

D. Arterial stiffness

Improving carotid-femoral pulse wave velocity measurement

E. Socio-economic variables

To evaluate the cost per patient/month in the control cases of conventional rehabilitation and extended tele-rehabilitation intervention.

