**SURVEYS**

| IPAQ (n) |  |
| --- | --- |
| PREDIMED (n) |  |
| HAD ANXIETY (n) |  |
| HAD DEPRESSION (n) |  |
| EQ-5D |  |
| FAGERSTRÖM (n) |  |

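### As printed, the HAD form scores every depression item and one anxiety item backwards, so a depression score taken literally from it has its direction reversed

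*Protocol*

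**What the plan says.** Section 4.2 lists among the secondary objectives "Demonstrate improved outcomes in psychological state". Sections 5 and 6.5 name the HAD as the anxiety-depression survey, and section 7.2 prints it with its scoring.

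- Four items are marked A for anxiety. Three name a symptom (tension, fear, worry), for example "I am tense or nervous (A". The fourth names its absence: "I can sit quietly and feel relaxed (A".
- Three items are marked D for depression: "I still enjoy what I once loved (D", "I can laugh and see the bright side of things (D", and one on feeling happy. All three describe good mood.
- Every item has the same four answers, rising from 0 for Never to 3 for Everyday.
- The Assessment has three bands. The lowest reads "If the result is between 0 and 7 it does not indicate a case of either anxiety or depression", the middle one (8 to 10) is a doubtful case, and the highest reads "If the result is above 11 it is probably a case in each of the subscales".

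The data collection notebook (Annex 1, Surveys, Visits 1 and 3) has one field for anxiety and one for depression, the latter labelled "HAD DEPRESSION (n". It has no fields for the single answers. Section 9.3 compares quantitative variables between groups by t-test or Mann-Whitney test, and within groups by the paired t-test or Wilcoxon signed-rank test.

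**The concern.** The item wording, the answer codes and the reading of the score do not fit together. A form that codes frequency from 0 to 3 and treats a high sum as illness works only for items that describe symptoms. Four of the seven printed items describe well-being, and the protocol gives no instruction to turn them round.

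At stake is the direction of the depression comparison and the sensitivity of the anxiety comparison. If totals are formed literally from the printed page, a programme that improves mood would be reported as worsening depression, and the reverse. Because the notebook keeps only totals, part of the damage could not be undone later unless the completed forms are kept.

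**Working it through.** **Inputs**, all from section 7.2: three D items, all positively worded; four A items, one of them positively worded; codes 0 to 3 on every item; bands 0 to 7, 8 to 10, and above 11, applied to each subscale.

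**Depression as printed.** D = d1 + d2 + d3.
- Good mood every day on all three items: 3 + 3 + 3 = 9, which is in the doubtful band.
- Never any of the three: 0 + 0 + 0 = 0, which is in the no-case band.

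**Depression after reversal.** Each item becomes 3 − d, so D* = 9 − D. Best mood scores 0 and worst scores 9. For two groups, D*(tele) − D*(control) = −[D(tele) − D(control)]. The size and spread of the difference are the same and only the sign changes. The two-sided p-value is therefore unchanged, and the conclusion drawn from it is reversed. The same holds for change within a group.

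**Anxiety as printed.** A = a1 + a2 + a3 + r, where r is the relaxed item.
- Most anxious consistent pattern: 3 + 3 + 3 + 0 = 9.
- Calmest consistent pattern: 0 + 0 + 0 + 3 = 3.
- Span: 9 − 3 = 6 points.

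**Anxiety after reversal.** A* = a1 + a2 + a3 + (3 − r) = A + 3 − 2r. The calmest pattern scores 0 and the most anxious 12, a span of 12. If all four items shift equally in severity, the printed score shows half the true change (6 against 12). Because A* depends on r, the total alone does not determine it. A recorded A = 6 corresponds to A* = 9 if r = 0 and to A* = 3 if r = 3.

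**Bands against attainable scores**, by enumerating every answer pattern on the printed items:

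| Subscale | Patterns | Maximum | 0 to 7 | 8 to 10 | exactly 11 (no band) | above 11 |
| --- | --- | --- | --- | --- | --- | --- |
| Depression | 4³ = 64 | 9 | 60 | 4 | 0 | 0 |
| Anxiety | 4⁴ = 256 | 12 | 190 | 61 | 4 | 1 |

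The single anxiety pattern above 11 needs a patient who is tense, fearful, worried and relaxed every day. Reversing the relaxed item makes 12 the score of a coherent, very anxious patient. Reversing the depression items leaves their maximum at 9, so reversal alone does not repair the top band there.

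**The case against.** Several points on the other side have weight.

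- **The consequence is conditional.** The sign reversal follows only if totals are taken literally from this page. A scoring rule may exist in a statistical analysis plan or scoring manual that is not at hand, and the text shows signs of translation, so patients may have seen other answer labels. This stands. It does not clear the protocol, because any such rule would still conflict with section 7.2 as printed.
- **The item count is uncertain.** Item numbering is damaged in the available text, so items may have been lost. This stands against the depression maximum of 9. It does not touch the backward coding of the four items that are shown, nor the gap at 11.
- **The bands have no stated role in the analysis.** This stands. The notebook stores numbers and no case/no-case analysis is specified, so the band faults have no demonstrated effect on a result.
- **The depression scores can be recovered.** Also true: with three uniformly reversed items, 9 minus the total is exact. It does not hold for anxiety.
- **HAD is one secondary measure among many.** It is missing from the list of variables in section 7.3, and EQ-5D also has an anxiety/depression question, so the psychological objective is not tied to HAD alone. This limits the weight of the point.

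A reader might infer that the case cut-off is out of reach on both subscales, or that no patient can ever be a depression case. The documents do not support either as a flat statement: anxiety reaches 12, and the depression limit depends on the seven items being the whole form.

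**Conclusion.** The point holds as a fault in the printed scoring. All three depression items and one of four anxiety items run against the direction in which the Assessment reads them. Scored as printed, depression runs from 9 (best mood) to 0 (worst), so its differences change sign at unchanged size, and the anxiety span for consistent responders shrinks from 12 points to 6. The gap at exactly 11 is certain. The unreachable top depression band holds only if the form has no further items.

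This rests on two assumptions: that the printed codes are those in use, and that no reversal is applied elsewhere. It would be going too far to say that the trial's depression result is reversed, because the protocol does not show how totals were actually computed. It would also be going too far to say that the trial's main conclusion is at risk, since the primary variable comes from the IPAQ. The correction is needed, but for a secondary outcome.

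**What to change.** 1. In section 7.2, state that the three depression items and the relaxed item are scored Never = 3 to Everyday = 0 before summing, and that the other three anxiety items keep the printed codes.
2. In Annex 1, record the answer to each item at Visits 1 and 3 as well as the two totals.
3. Establish how totals already entered were formed. If they were formed as printed, rescore them. Depression is 9 minus the recorded total, provided only these three items were used. Anxiety must be recomputed from the item answers on the completed forms.
4. Check the printed form against the one patients complete, and confirm that it contains every item the bands were meant for.
5. Make the bands contiguous, so that 11 belongs to one of them, and consistent with the attainable range of each subscale. Otherwise drop them and state that HAD is analysed only as a continuous score.

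The cost is a corrected page, a few extra notebook fields and a short scoring program. The only real effort is retrieving item answers for anxiety, which depends on the paper forms having been kept. Sample size and the primary analysis do not change.

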**c. Physical Activity Questionnaire (IPAQ)**

1. During the last 7 days, on how many days do I do intense physical activities such as heavy lifting, digging, aerobic exercise or fast cycling?

Days per week (please indicate the number)

No heavy physical activity (skip to question 3)

2. How much time in total did you usually spend doing vigorous physical activity on any one of those days?

Please indicate how many hours per day

Please indicate how many minutes per day

Don't know/not sure

3. During the last 7 days, on how many days did you do moderate physical activity such as carrying light weights, or cycling at a regular speed? Do not include walking

Days per week (indicate number)

No moderate physical activity (skip to question 5)

4. How much time did you usually spend in total in moderate physical activity on one of those days?

Indicate how many hours per day

Indicate how many minutes per day

Don't know/not sure

5. During the last 7 days, on how many days did you walk for at least 10 minutes at a time?

Days per week (give number)

No walking at all (skip to question 7)

6. How much time in total did you usually spend walking on any one of those days?

Indicate how many hours per day

Indicate how many minutes per day

Don't know/not sure

7. During the last 7 days, how much time did you spend sitting during a working day?

Please indicate how many hours per day

Please indicate how many minutes per day

Don't know/not sure

**EVALUATION:**

1. Walking: 3'3 METs x minutes of walking x days per week (e.g. 3'3 x 30 minutes x 5 days = 495 METs).

2. Moderate Physical Activity: 4 METs X minutes x days per week

3. Vigorous Physical Activity: 8 METs X minutes x days per week

Then add up the three values obtained:

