**Total = walking + moderate physical activity + vigorous physical activity**

**CLASSIFICATION CRITERIA:**

Moderate Physical Activity:

1. 3 or more days of vigorous physical activity at least 20 minutes per day.

2. 5 or more days of moderate physical activity and/or walking at least 30 minutes per day.

3. 5 or more days of any combination of walking, moderate or vigorous physical activity achieving at least a total of 600 METs*.

Vigorous Physical Activity:

1. Vigorous Physical Activity at least 3 days per week achieving a total of at least 1500 METs*.

2. 7 days of any combination of walking, moderate physical activity and/or vigorous physical activity, achieving a total of at least 3000 METs*.

** Unit of measurement of the test.*

RESULT: ACTIVITY LEVEL (tick as appropriate)

HIGH LEVEL

MODERATE LEVEL

LOW OR INACTIVE LEVEL

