## Variables

1. Principal Variable

Since the main objective is adherence to a physical activity program, the main variable of the study is the METS-minute/week measure. Obtained from the IPAQ questionnaire.

1. Secondary variables

1. Clinical data: age, sex, STEMI, NSTEMI, unstable angina, stable angina, number of vessels, number of stents, complete revascularisation, active smoking, former smoker, hypertension, dyslipidaemia, diabetes mellitus, left ventricular ejection fraction, beta-blockers, ACE inhibitors/ARBs, statins, dual antiplatelet therapy.

2. Socio-occupational data: active worker, days until return to work after discharge.

3. Physical examination: systolic blood pressure, diastolic blood pressure, heart rate, body mass index (BMI), waist circumference, hip circumference.

4. Exercise test: VO2max, exercise time, maximal heart rate, maximal blood pressure, recovery time, ST decline, angor.

5. Pulse wave velocity.

6. Analytical data: glucose, creatinine, total cholesterol, LDL cholesterol, HDL cholesterol, triglycerides, CRPus, HbA1c.

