# Statistical Analysis

## Sample size calculation

## The sample size is determined by the number of patients eligible for inclusion in the study who are seen in each hospital during the inclusion period. Thirty patients will be included in each of the following groups: control group, conventional rehabilitation group and telerehabilitation group. For the calculation of the power of the study, a 12% possible loss to follow-up has been estimated. Thus, accepting an alpha risk of 0.05 in a bilateral test with 27 subjects in the control group and 27 patients in the intervention group, the power of the hypothesis test is 95% to detect as statistically significant the difference between the mean of 5000 in the first group and the mean of 4000 in the second group after rehabilitation. Based on the potential impact of the telerehabilitation intervention on compliance with the physical activity recommendation at 10 months follow-up, and considering METs-minutes/week as the unit of measurement, it has been estimated that patients in the intervention group will perform 5000 METs-minutes/week while in the conventional rehabilitation group they will perform 4000 METs-minutes/week. It is estimated that physical activity in the non-rehabilitation group will be significantly lower.

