## Economic evaluation: cost-effectiveness analysis

The study includes a cost-effectiveness analysis to assess the costs and impact on health-related quality of life of the telerehabilitation intervention compared to in-hospital rehabilitation and the control group. The cost analysis will be carried out from the funder's perspective, including direct health care costs (pathology-related emergency visits, hospitalisations for the same cause, diagnostic and therapeutic tests such as revascularisations...) during follow-up. It will also include the costs derived from the intervention, which in the case of conventional rehabilitation, the programd schedule includes 16 rehabilitation visits, 8 rehabilitation sessions (with a physiotherapist, a nurse and a nursing assistant per session) and 8 educational talks. In the telerehabilitation group, the schedule includes 4 rehabilitation visits, 3 sessions (with a physiotherapist and a nurse) and 4 educational sessions. Unscheduled visits and sessions during the follow-up will also be included. The unit costs will be obtained from the Generalitat Valenciana catalogue.

Additionally, an analysis will be performed from a social perspective, including also indirect health care costs due to lost productivity of the patient (number of sick leaves and time to return to work after the event). Indirect costs will be reported by the patient in the follow-up data collection logbook. Effectiveness will be assessed by the physical activity performed by the patient, reported by the patient at the end of the follow-up, measured in METs-minutes/week.

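### The primary IPAQ score is summed with no upper limit on reported time, so with 27 patients per arm a single extreme self-report can move an arm mean materially.

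*Protocol*

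**What the plan says.** Section 7.3 (Variables) states that "the main variable of the study is the METS-minute/week measure. Obtained from the IPAQ questionnaire".

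Section 7.2 (Measuring instruments, IPAQ) asks for days per week and for usual time per day, entered freely as hours and minutes, for example "How much time did you usually spend in total in moderate physical activity on one of those days". Its Evaluation part then gives three products:

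- "Walking: 3'3 METs x minutes of walking x days per week"
- "Moderate Physical Activity: 4 METs X minutes x days per week"
- "Vigorous Physical Activity: 8 METs X minutes x days per week"

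The score is their plain sum: "Total = walking + moderate physical activity + vigorous physical activity". The protocol gives no limit on minutes, no check that the three times fit into one day, and no handling of an implausible total.

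The data collection notebook (Annex 1, Visits 1 and 3) has one numeric field for the IPAQ and none for minutes or days.

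Section 9.1 plans on a difference in means of this score: "the power of the hypothesis test is 95% to detect as statistically significant the difference between the mean of 5000 in the first group", against 4000 in the other, with 27 analysed per arm. Section 9.3 uses a t-test, with Mann-Whitney when parametric assumptions fail, and multiple linear regression for the significance and size of the intervention effect. Section 9.4 takes as its effectiveness measure the physical activity "reported by the patient at the end of the follow-up, measured in METs-minutes/week".

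**The concern.** The score multiplies whatever time the patient writes down by up to 8 and by up to 7 days. Four one-hour walks a week score 3.3 x 60 x 4 = 792. A patient who counts a working day as moderate or vigorous activity can score well over 10,000. The planned arm means are 4000 and 5000, so in an arm of 27 one such record carries real weight in the mean and more in the variance. Every mean-based result is exposed: the reported difference and its interval, the regression estimate, and any cost per METs-minute/week.

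Two features make this hard to repair later. The notebook stores only the total, so minutes could be truncated only by returning to the completed questionnaires. And section 6.1 says that patients and professionals are not blinded and does not list the surveys among the masked assessments, so a decision about an outlying score taken after the data are in could be taken knowing the arm.

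**Working it through.** **Inputs.** From section 9.1: 27 per arm, two-sided alpha 0.05, means 5000 and 4000, power 95%. From section 7.2: weights 3.3, 4 and 8. The protocol states no SD. The hours reported below are illustrative assumptions.

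**The plan's own figure.** Without an SD the 95% cannot be reproduced directly, so I solved for the SD. With noncentrality 1000 / (SD x sqrt(2/27)) and 52 degrees of freedom, 95% power requires an SD of about 1000. Putting SD = 1000 back gives 95.0%. SD 1000 is used below.

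**Scores under the written rule.**

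- Record A: 30 min walking x 7 days plus 8 h moderate x 5 days. 3.3 x 30 x 7 + 4 x 480 x 5 = 693 + 9600 = 10,293.
- Record B: 30 min walking x 7 days plus 6 h vigorous x 5 days. 693 + 8 x 360 x 5 = 693 + 14,400 = 15,093.
- Truncated at 180 min per activity per day, A = 693 + 3600 = 4293 and B = 693 + 7200 = 7893.

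**Shift of an arm mean.** If the record replaces an average patient, the shift is (score - planned arm mean) / 27.

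| Record | Score | Control (4000) | Intervention (5000) | Size relative to 1000 |
| --- | --- | --- | --- | --- |
| A, as written | 10,293 | 233 | 196 | 20 to 23% |
| B, as written | 15,093 | 411 | 374 | 37 to 41% |
| A, truncated | 4293 | 11 | -26 | 1 to 3% |
| B, truncated | 7893 | 144 | 107 | 11 to 14% |

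A record in one arm only changes the expected difference by the full shift. In the control arm, A reduces it to 1000 - 233 = 767 and B to 1000 - 411 = 589.

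**Power with one such record in each arm** (simulation, normal data, SD 1000, 26 other patients per arm). The expected difference is then 1000 x 26/27 = 963, so nearly all the loss comes from the inflated variance.

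| Record in each arm | t-test | Mann-Whitney |
| --- | --- | --- |
| None | 95% | about 94% |
| A, as written | about 71 to 72% | about 91% |
| B, as written | about 16% | about 91% |
| A, truncated | about 94% | about 93% |
| B, truncated | about 88% | about 91% |

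**What it takes to move a mean by a third of the planned effect.** The score must exceed the arm mean by 27 x 1000/3 = 9000. At 7 days a week from one activity alone, that is 7.7 h/day moderate, 3.9 h/day vigorous or 9.4 h/day walking in the control arm, and 8.3, 4.2 or 10.1 h/day in the intervention arm.

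**The case against.** **Cleaning rules usually belong in the SAP.** Section 12.2 refers to one that is not shown. This is fair for range checks and queries in general. Here, however, the protocol writes the scoring formula itself, without a limit, and designs a notebook that discards the minutes and days a later truncation would need.

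**The planned test has a fallback.** This stands for the p-value: Mann-Whitney keeps about 91% power in both examples, and one score above 10,000 in an otherwise normal arm of 27 would be an obvious departure from normality. The fallback does nothing for the mean difference, the regression or the cost-effectiveness measure.

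**Long hours may be genuine, and nothing shows that they are common.** Also fair. The questionnaire counts heavy lifting and digging, return to work is a secondary objective, and no distribution of scores is given. A reader might infer that the trial's result will be decided by a few implausible reports; the protocol does not support that.

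**A reader might also overstate the size.** Dividing the moderate component alone by the arm size gives 9600/27 = 356, which suggests that any long report moves the mean by more than a third of the effect. That calculation leaves the patient an average arm score from other activity, whereas record A has only 693 points elsewhere; its shift is 196 to 233.

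**A cap may penalise walking, the activity the intervention promotes.** At 180 min/day walking tops out at 3.3 x 180 x 7 = 4158, below the planned 5000, which by walking alone needs 5000 / (3.3 x 7) = 216 min/day. The point is limited, because section 6.4 asks for exercise four times a week and the score sums three activities. It is still a reason to check the planned means on the truncated scale.

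**Conclusion.** The point holds as a weakness in a rule the protocol fixes, not as a contradiction and not as a failure of the primary test. With 27 per arm, one extreme self-report can shift an arm mean by 20 to 23% (record A) or 37 to 41% (record B) of the planned 1000. One such record in each arm lowers t-test power from 95% to about 71 to 72% or about 16%.

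These figures rest on three assumptions: the record replaces an average patient, the SD is the 1000 implied by the stated power, and the hours are illustrative. The frequency of such reports is unknown. The exposure is confined to the mean difference, the regression and the cost-effectiveness measure. A prespecified limit is worth adding because it is cheap now and hard to add neutrally later.

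**What to change.** 1. In Annex 1, record days and minutes per day for walking, moderate and vigorous activity alongside the IPAQ total.
2. In section 7.2 (IPAQ, Evaluation), state before any outcome data by arm are seen that daily minutes are truncated per activity before multiplying, and that daily times which cannot together fit into a waking day are queried. The 180 minutes used above is an example; the limit is the investigators' choice, and what matters is that it is fixed in advance.
3. Use the truncated score for the t-test, the regression and the cost-effectiveness measure, and report the untruncated score as a sensitivity analysis.
4. Check the planned means of 4000 and 5000 on the truncated scale and restate them if needed.

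The cost is a few notebook fields, a short addition to the scoring section and a line of code. The downside is that real activity above the limit is not credited. Truncation also reduces the problem without removing it: at 180 minutes in all three activities on 7 days the score can still reach 180 x 7 x (3.3 + 4 + 8) = 19,278.
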